### Data management and analysis

A research assistant will review the integrity and quality of the data to upload to the big data platform. The uploaded data will be further reviewed by the epidemiologists of the Clinical Research Center for Endemic Disease of Shaanxi province. Whilst unqualified data will be reacquired. Of note, the data output will be checked weekly.

Simultaneously, all the data will be uploaded to the official website of the Chinese Clinical Trial Registration Center for review. Based on previous findings and recommendations of the Health Services Standards Research Committee, baseline data and hybrid models will be analyzed in different categories and time-to-event analyses will be performed on subsequent data. Multiple inputs will be applied to deal with missing values.

## Limitations

The fact that KD has a complicated etiology, therefore, it is difficult to distinguish its clinical symptoms from those of DCM.Limitations of this study include selection bias, as it includes only 18 to 70-year-olds and only the Chinese population, which may lead to the need to confirm the results of multinational studies.Of note, presently we do not know how many participants will continue to participate or leave this study, due to various reasons i.e., relocation, refusal to join, and other diseases and deaths. If there is a loss, we will immediately find the cause and remedy it. If it cannot be remedied, we will follow the last-observation-carried-forward (LOCF) method. Moreover, we will follow up with the participants to ensure the continuity of the data.

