**Methods:**

This cohort study consists of two parts. Though the first part includes 300 participants, however, recruiting will be continued for the eligible participants. After rigorous screening, the blood samples, stools, electrocardiograms, and ultrasonic cardiogram data would be collected from participants to elucidate the relationship between gut flora and host. The second part includes a prospective follow-up study for every 6 months within 2 years. Finally, deep mining of big data and rapid machine learning will be employed to analyze the baseline data, experimental data, and clinical data to seek out the new biomarkers to predict the pathogenesis of Keshan disease.

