### Study objects

This study will recruit 300 participants among which 200 participants will be from Keshan disease-prone areas in Shaanxi Province and the other 100 participants were from five non-ward areas through a random consultation. This cohort will include the suspected KD (50 cases), LKD (50 cases), CKD (50 cases), normal ward control (50 cases), DCM (50 cases), and normal non-ward control (50 cases) (Table 1). According to our estimation, the final sample size could reach about 300 participants. The recruitment will start from January 1, 2020, to December 31, 2020, and the participants with satisfying eligibility criteria will be included in our study.

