### Outcomes

#### Minor outcome measures

The minor outcome will include healthy people or suspected KD develop into KD, and LKD develops into CKD.

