#### Major outcome measures

The main outcomes will include acute Keshan disease attack, severe heart failure, perioperative period, and death.

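### The rules for participants who leave are not reconciled, and last observation carried forward, if applied to the event outcomes, would understate progression

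*Protocol article*

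**What the plan says.** All references are to the protocol article.

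- **Exclusion criteria:** the last item excludes participants who are unwilling to go on with the study.
- **Data management and analysis:** "time-to-event analyses will be performed on subsequent data", and "Multiple inputs will be applied to deal with missing values". The second phrase most naturally means multiple imputation, although the article does not use that term.
- **Limitations:** the number who will stay is unknown, "due to various reasons i.e., relocation, refusal to join, and other diseases and deaths". The cause of a loss will be sought and remedied. Failing that, "If it cannot be remedied, we will follow the last-observation-carried-forward (LOCF) method".
- **Major outcome measures:** "The main outcomes will include acute Keshan disease attack, severe heart failure, perioperative period, and death".
- **Minor outcome measures:** "The minor outcome will include healthy people or suspected KD develop into KD, and LKD develops into CKD".
- **Abstract, Methods:** the second part is "a prospective follow-up study for every 6 months within 2 years". The follow-up phase section adds monthly contact by phone or messaging.

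No section assigns a rule to particular variables or outcomes, and none says how LOCF treats a participant who has died.

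**The concern.** A time-to-event analysis censors an event-free leaver at the last time the status was known. LOCF gives the same person a status at month 24 and treats it as observed. Exclusion removes the person altogether. These are three different estimators, so the result would depend on which sentence the analyst follows.

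For an outcome counted as reached or not reached by month 24, carrying an event-free status forward can miss an event but cannot add one. It also treats a guessed value as known, which overstates precision. The outcomes exposed are the transitions in the minor outcome and, on one reading, the major outcomes. Death appears both as a major outcome and among the reasons for leaving. The follow-up part rests on these outcomes, and with 50 participants per group the event counts will be small.

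**Working it through.** **No figure to reproduce.** The article gives no event rate, loss rate or power calculation for follow-up. The group sizes agree with each other (6 × 50 = 200 + 100 = 300). The contradiction is textual, and the arithmetic below only shows the direction of the bias and its plausible size.

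**Inputs**
- Four visits, at 6, 12, 18 and 24 months: an interpretation of the six-monthly schedule over two years.
- Two-year progression risk p = 20%, constant over intervals: assumed.
- Two-year loss d = 10%, 20% or 30% (the probability of leaving if no event occurs), constant over intervals, with loss coming before the visit: assumed.
- Hazard in leavers after leaving, m = 1, 2 or 3 times that of stayers: assumed.

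**Formulas**
- Per-interval risk: h = 1 − (1 − p)^(1/4) = 1 − 0.8^0.25 = 0.0543.
- Per-interval loss: l = 1 − (1 − d)^(1/4).
- Fraction still present and event-free after each interval: q = (1 − h)(1 − l).
- LOCF proportion at month 24: h(1 − l) × (1 − q⁴)/(1 − q).
- Censoring (Kaplan-Meier): 1 − (1 − h)⁴ = p = 20.0% at any loss level.

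**Worked case, d = 20%.** Here l = 0.0543 and q = 0.8944. The sum (1 − q⁴)/(1 − q) = 0.36/0.1056 = 3.410. LOCF = 0.0543 × 0.9457 × 3.410 = 17.5%. The relative shortfall is 17.5/20.0 − 1 = −12.5%.

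| Loss d | LOCF | Truth, m = 1 | Truth, m = 2 | Truth, m = 3 | LOCF relative to truth (m = 1, 2, 3) |
|---|---|---|---|---|---|
| 10% | 18.8% | 20.0% | 21.1% | 22.1% | −6%, −11%, −15% |
| 20% | 17.5% | 20.0% | 22.2% | 24.2% | −12.5%, −21%, −28% |
| 30% | 16.2% | 20.0% | 23.4% | 26.4% | −19%, −31%, −39% |

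Varying p from 10% to 30% with m = 1 barely changes the relative shortfall: 6.1-6.3%, 12.3-12.7% and 18.8-19.3% at the three loss levels.

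**In events.** In a group of 50, a 20% risk is 10 progressions. LOCF would show on average 50 × 0.188 = 9.4, 50 × 0.175 = 8.75 or 50 × 0.162 = 8.1.

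**Exclusion gives another answer.** Take d = 20%, m = 1, and suppose every leaver is someone who refuses to go on and is dropped. The fraction lost event-free is l × 3.410 = 18.5%, so the proportion among those kept is 17.5/(100 − 18.5) = 21.5%. Under the same assumptions, exclusion, censoring and LOCF give 21.5%, 20.0% and 17.5%.

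**Limit of censoring.** When leavers progress faster, censoring is also too low (20.0% against 22.2% at d = 20%, m = 2), though by less than LOCF. That is why a sensitivity analysis is needed as well.

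**Deaths.** If a group of 50 has 5 deaths (10%) and all are recorded as event outcomes, the proportion is 10%. If half are treated as losses and carried forward alive, it is 2.5/50 = 5%. If all are, it is 0%. The article does not say that this will happen; it leaves it open.

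**The case against.** The strongest defence is that the sentences can be read together: time-to-event analysis for the outcomes, multiple imputation for scattered gaps, and LOCF only for repeated measurements such as ultrasound, laboratory and flora values after drop-out. That reading is possible, so it would be too strong to say the sections cannot both be followed. But the article does not state it, and it would leave LOCF on repeated measures, where the direction of its bias is not even known. The exclusion item may likewise be meant for enrolment only; its wording does not settle that.

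Several stronger readings are tempting and are not supported:

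- **That LOCF applies to everyone who leaves.** It applies only where a loss cannot be remedied, and those who refuse to go on have the separate exclusion rule.
- **That deaths will be recorded as survivors.** The list containing deaths explains why retention is unknown; it does not define the scope of LOCF. Death is a main outcome, contact is monthly, and the cause of each loss is to be sought. A known death can be counted as an event under the outcomes section.
- **That the disease moves only one way, so every carried-forward stage is at or below the truth.** The article does not say this, and suspected cases are only preliminarily diagnosed. The downward direction holds for event counts as defined, not for stage in general.
- **That the under-count is largest in the sickest groups, or that flora associations will shrink.** Neither is computed here nor stated in the article.

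It is also fair that the sizes rest on assumed rates, with the largest depending on the least supported input, the leavers' excess hazard. The direction for an event outcome does not depend on those rates.

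**Conclusion.** The concern holds in limited form. The exclusion criteria, the analysis section and the limitations section give unreconciled rules for participants who leave. If LOCF is used for the event outcomes, progression is biased downward relative to censoring. At an assumed 20% two-year risk over four visits with non-informative loss, the relative shortfall is about 6%, 12-13% and 19% at 10%, 20% and 30% loss. It is larger if leavers progress faster. Under-counting of deaths is conditional on their being handled as losses.

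The baseline comparison of six groups and the search for diagnostic markers in the first part are untouched. This should be fixed before the follow-up data are analysed; it does not undermine the study as a whole.

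**What to change.** 1. In Limitations, remove LOCF for the event outcomes.
2. State that every known death counts as a main-outcome event and is never a missing value.
3. Amend the exclusion item so that those who withdraw stay in the analysis up to withdrawal.
4. For the major outcomes, censor event-free leavers at the last monthly contact. For progression, censor at the last clinic assessment and treat death as a competing event.
5. For repeated measures, use mixed models on all observed visits. Reserve multiple imputation for missing covariates, and name it as such.
6. Add one sensitivity analysis in which leavers have a higher hazard than stayers, for example 2 and 3 times.

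The cost is wording in the protocol and the SAP and a little more analysis. The twice-yearly clinics and monthly contacts that supply the censoring dates are already planned.

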## Discussion

Despite having ample amounts of clinical cohorts of cardiovascular diseases in China, few gut flora studies have been focused on KD. The innovation of the present study lies in the combination of different methodologies which aim at collecting objective data concerning the characterization of the gut flora in KD patients, to highlight the variation in gut flora or mutual development of KD (normal ward, suspected KD, LKD, CKD), and to clarify the gut flora diversity between KD and DCM. Moreover, metagenomics metabolomics and metagenomics data will allow us to collect detailed information about the interaction between gut flora and KD along with the functional changes of gut flora in KD patients. Additionally, the inclusion of research tools of gut flora function and big data technology allow us to screen out novel biomarkers for early diagnosis and the molecular changes in the development of KD. Thus, it will provide a complete guideline to a novel perspective for the clinical treatment of KD. By looking at the defined causes of KD, we will be able to assess huge economic and social benefits for our country, by enhancing the chances of early prevention of KD, improving the prognosis of patients with KD, and even laying the foundation for the ultimate elimination of KD.

Though in recent years, many researchers have conducted extensive researches on the effects of genetic variation, gut flora, and its metabolites on cardiovascular diseases [20–23]. However, in the present study, it has been suggested that some people may have more than two risk factors, which attracts more researchers to search for common causes. The prospective study allows us to find the causes of KD from selenium deficiency, viral infection, nutritional deficiency, and other incentives. The fact our previously reported study could only determine a few aspects, however, here we attempted to identify the major cause. Furthermore, the implication of the perspective of genetics allows assessing that KD has certain heredities. Therefore, as a further strategy to determine the etiology of KD, we plan to establish a biological sample library to collect adequate samples and accumulate a large amount of useful data to fully prepare for later research.

Additionally, our team will invite each of the small and medium-sized hospitals in Shaanxi province to share their experience at the Clinical Research Center for Endemic Disease of Shaanxi province**,** to conduct a panel discussion of KD in every quarter. Moreover, we will regularly arrange the KD special lectures in the areas with high incidences to standardize the training of clinical centers in each hospital. Our team is very keen to help small and medium-sized hospitals to standardize the diagnosis and treatment of KD through the above-mentioned methods. In conclusion, through its multidisciplinary approach, the KD prospective cohort study allows the evaluation of risk factors for the development of KD and will also improve our understanding of the underlying pathogenic mechanism. Nevertheless, we also aim to spread the knowledge of KD to the patients to prevent KD in advance.

## Data Availability

The datasets used and/or analyzed during the current study are available from the corresponding author on reasonable request.

## Abbreviations

KD: Keshan disease
ECG: Electrocardiogram
UCG: Ultrasonic cardiogram
CKD: Chronic Keshan disease
TMAO: Trimethyl-n-oxide
SCFA: Short-chain fatty acid
CRC: Cardiovascular research center
LKD: Latent Keshan disease
LOCF: Last-observation-carried-forward
IPAQ: Physical activity questionnaire
CBC: Hematological parameters
HDL: High-density lipoprotein cholesterol
LDL: Low-density lipoprotein cholesterol
